## Abstract

**Background::**

Failed intubation and ventilation during cesarean deliveries are important causes of anesthetic-related maternal mortality. Due to the physiological changes in airway anatomy, parturient had higher incidences of difficult airway than non-obstetric population. Accurate airway assessment is the first step and the most important in airway management. However, the common clinical screening tests, shown low sensitivity and specificity with a limited predictive value. Ultrasound is a quick, noninvasive, inexpensive tool, with the advancement of ultrasound technology, modern ultrasound machine is more portable with better resolution and enhanced tissue penetration, provide better imaging in tissues like epiglottis, vocal cords, ring-shaped membrane, and can be used in airway assessment. Here, the aim of the current study was to find whether preoperative ultrasound assessment of neck anatomy can predict difficult airway in parturient, and provide new ideas and a theoretical basis in the airway management of obstetric anesthesia.

**Methods::**

This is a prospective, observational single-blinded study in a single-center. Subjects will be recruited from patients aged from 18 to 60 years, gestational age ≥ 36 weeks, scheduled for cesarean section under general anesthesia and tracheal intubation. Ultrasound measurement will be performed to detect anterior cervical soft tissue thickness at five anatomical levels (hyoid bone, epiglottis, cricothyroid membrane, thyroid isthmus and suprasternal notch) in the upper airway. The thickness of the soft tissue in the front of the neck and clinical airway measurements will be compared between the “easy intubation” and “difficult intubation” group divided by Cormack–Lehane grade. Receiver-operating characteristic curves were used to determine the sensitivity and specificity of “difficulty prediction capability” of each sonographic and physical measurements. Clinical factors associated with difficult intubation will be determined by univariate analyses. Multiple logistic regression analysis performed to determine independent predictors of difficult intubation.

**Conclusions::**

The study outlined in this protocol will explore the possibility of ultrasound for predicting difficult airway in obstetric anesthesia. This may provide new insight into the practice of airway management.

**Trial registration::**

Chinese Clinical Trial Registry, ChiCTR1800018949.

## Introduction

1

In obstetric anesthesia, difficult airway is frequently unexpected. Failed intubation and ventilation during cesarean deliveries are important causes of anesthetic-related maternal mortality.^[1,2]^ Due to the physiological changes in airway anatomy like tracheal edema and obesity, parturient had higher incidences of difficult airway than non-obstetric population. The statistics in the USA indicated the most deaths of parturient were attributed to airway management difficulties, failure to provide adequate oxygenation and carbon dioxide removal, lead to life-threatening complications.^[3]^ With the implementation of the “2-child policy” in China, the number of elderly and critically ill women has increased dramatically,^[4]^ more parturient need to receive cesarean section with general anesthesia, that increases the risk of a difficult airway and maternal mortality.

Airway assessment is an essential component for the anesthesiologist. Accurate airway assessment is the first step towards avoiding potential complications and should always be the most important in airway management. Available guidelines suggest the clinical evaluation of Mallampati classification, thyromental distance, upper lip bite test, interincisor distance, BMI could be used to predict the risk of difficult airway.^[5,6]^ However, despite these clinical tests, showed low sensitivity and specificity with a limited predictive value, especially if only a single assessment method is used.^[7,8]^

During the last few years, perioperative ultrasound has been widely used in anesthesiology and intensive care practice for diagnostic and therapeutic relevance, such as nerve block, vascular cannulation, and focused cardiovascular ultrasound examination (FoCUS).^[9,10]^ With the advancement of ultrasound technology, modern ultrasound machine is more portable with better resolution and enhanced tissue penetration, provide better imaging in tissues like epiglottis, vocal cords, ring-shaped membrane. Ultrasound is a quick, noninvasive, inexpensive tool and can provide accurate information in airway assessment. With characteristics of non-radiating is the best application in obstetric anesthesia compared with computerized tomography (CT) and X-ray. It has been reported in the literature that ultrasound can help determine the position of the tracheal tube and evaluate the position of the laryngeal mask and predict difficult airways.^[11]^ Recently, studies had reported that ultrasound can be taken into consideration as a predictor of difficult laryngoscopy by measuring the anterior neck soft-tissue thickness.^[12,13]^

However, there is limited data to provide high-level scientific evidence of the potential role of ultrasound on assessing the airway in parturient. The methodologically rigorous trials are important to determine the use of ultrasound in predicting difficult airway, and to provide new ideas and a theoretical basis in the airway management of obstetric anesthesia.

## Objective

2

The aim of the current study was to find whether preoperative ultrasound assessment of neck anatomy can predict difficult airway in parturient, by analysis correlations between ultrasound measurements of anterior cervical soft tissue thickness at 5 anatomical levels (hyoid bone, epiglottis, cricothyroid membrane, thyroid isthmus and suprasternal notch) in the upper airway, and the Cormack–Lehane grade. The secondary objective was to determine whether clinical screening tests are independent predictors of difficult airway.

We consider that ultrasound airway assessment have higher specificity and sensitivity than traditional clinical test in predict difficult airway.

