### Sample size and study power

3.9

Optimal sample size has been evaluated based on a statistical power of 80% and a significance level of 0.05 (two-tailed). According to the previous study, in obese surgical patients, an incidence of difficult intubation was about 10% to 20%.^[16,17]^ Ultrasound measurements should predict at least 80% difficulty intubations (Cormack–Lehane grade ≥ 2b), additionally, 20 events are needed to derive two or more correlates in a logistic regression model.^[18]^ It is estimated that a sample size of 106 will be needed, to adjust the possibility 20% of dropout, 127 subjects will be recruited into the study.

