### Statistics

3.10

After the intubation is complete, all data will be collected. Data analysis was performed using the statistical software SPSS 20.0. The thickness of the soft tissue in the front of the neck and clinical airway measurements will be compared between the “easy intubation” and “difficult intubation” group. ROC curves were used to determine the sensitivity and specificity of “difficult prediction capability” of each sonographic and physical measurements. Clinical factors associated with difficult intubation will be determined by univariate analyses. X^2^ analysis will be used for categorical or binary variables, unpaired t-test analysis was used for continuous variables. Multiple logistic regression analysis performed to determine independent predictors of difficult intubation. The results were averaged, and the data are presented as mean ± SD for each variable with continuous data. Categorical data were expressed as frequencies (%). All variables with P value along with their respective odds ratio and 95% confidence intervals were obtained. *P* value <.05 will be considered statistically significant.

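### The plan expects ultrasound to beat clinical tests on sensitivity and specificity, but no stated analysis compares the two

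*Protocol article*

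**What the plan says.** The Objective section gives two formal objectives, and neither is comparative. The main one: "The aim of the current study was to find whether preoperative ultrasound assessment of neck anatomy can predict difficult airway in parturient". The secondary one: "The secondary objective was to determine whether clinical screening tests are independent predictors of difficult airway". A directional expectation follows: "We consider that ultrasound airway assessment have higher specificity and sensitivity than traditional clinical test in predict difficult airway". It names no ultrasound level, clinical comparator, cut-off or size of difference.

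Section 3.10 (Statistics), and the Methods part of the Abstract, list three kinds of analysis:

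- Group comparison: "The thickness of the soft tissue in the front of the neck and clinical airway measurements will be compared between the" easy and difficult intubation groups, by chi-square for categorical variables, while "unpaired t-test analysis was used for continuous variables".
- Accuracy: "ROC curves were used to determine the sensitivity and specificity of" each sonographic and each physical measurement.
- Regression: "Multiple logistic regression analysis performed to determine independent predictors of difficult intubation".

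Section 3.9 (Sample size and study power) uses 80% power, a two-sided 5% level, a difficult-intubation incidence of 10% to 20%, a target that ultrasound should predict at least 80% of difficult intubations, and a rule of 20 events for the logistic model. It arrives at 106 women, or 127 with dropout. It gives no accuracy for a clinical test and no difference to detect.

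**The concern.** To say that one test has higher sensitivity and specificity than another is to claim a difference between them. None of the three listed analyses estimates or tests that difference. The group comparisons and the regression ask whether each predictor is associated with difficult intubation. The ROC curves describe each measurement on its own. The expectation could then be judged only by seeing which AUC or sensitivity came out larger, or by noting that one predictor reached P < .05 and another did not. Neither is a test of difference.

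The comparison is also undefined. Sections 3.4 and 3.5 give five ultrasound levels, measured with normal and extended neck, and about ten clinical measures. Any pair could be chosen after the results are seen. At stake is a published statement that ultrasound outperforms bedside screening, resting on a gap that chance could produce.

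**Working it through.** **1. The plan's own sample size, and whether it contains the comparison.** The event rule gives 20 / 0.20 = 100, 20 / 0.15 = 134 and 20 / 0.10 = 200. A total of 106 would need an incidence of 20 / 106 = 18.9%. The recruited number follows as 106 × 1.2 = 127.2. So 106 does not come exactly from the stated incidences. For this point, what matters is that every stated input concerns ultrasound alone or the event count.

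**2. Inputs for the missing comparison.**

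- From section 3.9: 106 women and an incidence of 10% to 20%. Then 106 × 0.10 = 10.6, 106 × 0.15 = 15.9 and 106 × 0.20 = 21.2, or about 11, 16 and 21 difficult cases.
- Assumed, because the documents give no value: AUC 0.80 for ultrasound and 0.70 for the clinical test, and a correlation r of 0.3 to 0.5 between the two AUC estimates.

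**3. Formulas.** Hanley–McNeil variance of one AUC, with n1 difficult and n0 easy cases, a = A/(2 − A) and b = 2A²/(1 + A):

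Var(A) = [A(1 − A) + (n1 − 1)(a − A²) + (n0 − 1)(b − A²)] / (n1 × n0)

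SE of the paired difference = √(s1² + s2² − 2·r·s1·s2). Half-width = 1.96 × SE. Power = Φ(difference/SE − 1.96).

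**4. One case in full: 16 difficult, 90 easy, r = 0.5.**

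- A = 0.80: (0.16 + 0.40 + 6.329) / 1440 = 0.004784, so s1 = 0.0692.
- A = 0.70: (0.21 + 0.727 + 7.696) / 1440 = 0.005995, so s2 = 0.0774.
- SE = √(0.004784 + 0.005995 − 2 × 0.5 × 0.0692 × 0.0774) = 0.074.
- Half-width = 0.144. Power = Φ(0.10/0.0736 − 1.96) = Φ(−0.60) = 27%.

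**5. The range.** SE and half-width are for 0.80 vs 0.70.

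| Difficult cases | r | SE | 95% half-width | Power, 0.80 vs 0.70 | Power, 0.90 vs 0.70 |
|---|---|---|---|---|---|
| 11 | 0.3 | 0.103 | 0.20 | 16% | 56% |
| 11 | 0.5 | 0.088 | 0.17 | 21% | 69% |
| 16 | 0.3 | 0.087 | 0.17 | 21% | 71% |
| 16 | 0.5 | 0.074 | 0.14 | 27% | 83% |
| 21 | 0.3 | 0.077 | 0.15 | 25% | 81% |
| 21 | 0.5 | 0.065 | 0.13 | 33% | 91% |

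**6. Sensitivity itself.** Take the plan's 80% for ultrasound and an assumed 60% for a clinical test, with within-woman correlation 0 to 0.3. Exact McNemar power is about 3% to 5% with 11 difficult cases and about 18% to 21% with 21.

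**The case against.** The strongest reply concerns the status of the sentence. It follows two formal objectives that are not comparative, opens as an opinion, and has no counterpart in the outcome list or the sample size. The Conclusions of the Abstract describe the study as exploratory. A reader might infer that the trial's main question goes unanswered. The documents do not support that: the listed analyses do address both formal objectives. This lowers the severity but does not remove the mismatch, because the expectation stands in the Objective section.

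A second reply is that the choice of paired test could sit in an analysis plan that is not shown. That is fair for the name of the test. But the article does list its analyses and its sizing basis, and none is comparative.

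Two further inferences go too far:

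- A reader might infer that the study cannot show whether ultrasound adds to the clinical tests. If both kinds of measure enter one logistic model, the adjusted ultrasound odds ratio does test association beyond them. The article does not say that they enter together, and such a model would still not show higher sensitivity and specificity.
- A reader might infer that picking the best ultrasound level favours ultrasound. About ten clinical measures can be selected just as freely, so the direction of any bias is not established.

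**Conclusion.** The point holds as a mismatch between a stated expectation and the planned analyses: the plan expects higher accuracy for ultrasound and states nothing that compares it with clinical tests. This does not depend on any assumed number.

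The size does. Under AUCs of 0.80 versus 0.70, 11 to 21 difficult cases among 106 women and r of 0.3 to 0.5, observed AUC gaps of up to about 0.13 to 0.20 could not be told apart from no difference, and power is about 16% to 33%. A reader might take from the table that a gap of 0.20 gives 83% power. That is one cell; across the same range it is 56% to 91%.

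Severity: should-fix. Both formal objectives remain analysable.

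**What to change.** In section 3.10:

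1. Name in advance one ultrasound measurement (level and neck position) and one clinical comparator (a single test or a fixed score).
2. Report their paired AUC difference with a 95% CI by the DeLong method. Conclude that ultrasound is higher only if the CI excludes zero, and word that conclusion as higher AUC.
3. If no such comparison is wanted, restate the sentence in the Objective section as exploratory and present the separate ROC curves as descriptive.
4. If added value is to be claimed, state that ultrasound and clinical measures enter the same logistic model.

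The cost is protocol wording and one extra analysis on data already being collected. The downside is that, at the planned size, the comparison will probably be inconclusive, and the report would have to say so.

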## Methods

3

### Ethics approvals and registration

3.1

Ethic approval for this study has been obtained from the Medical Ethics Committee of Sichuan Academy of Medical Sciences & Sichuan Provincial People's Hospital (No. 2018-240). The trial was registered at Chinese Clinical Trial Registry (ChiCTR1800018949). Participating sites obtained written informed consent by participating patients or their legal surrogates in accordance with local/ national legislations. Fully data will be upload on the Clinical Trial Management Public Platform. Results will be published in peer-reviewed journals and disseminated at international conferences.

### Study design

3.2

The flowchart of this trial is in Figure 1. This is a prospective, observational single-blinded study being conducted in a single center. The study will observe patients scheduled for cesarean section under general anesthesia in the operating theatre of the Sichuan Provincial People's Hospital, Chengdu, China from January 2020 to January 2021.

**Figure 1 F1:**
[figure not shown]
Flow chart of the study.

### Recruitment of patients and blinding

3.3

The subjects will be recruited from the department of obstetrics surgical ward in Sichuan Provincial People's Hospital. Patients were included in the study after obtaining informed consent. Both Chinese and English written informed consent in will be obtained from every participant. Once participants were enrolled in the study, they will be anonymized by an identification code. The subjects can voluntarily withdraw from the trial at any time. Preoperative evaluation and ultrasound examination will be performed by a single trained investigator skilled with airway ultrasound examination. The anesthesiologists perform the laryngoscopy and endotracheal intubation, they will be blinded to the findings of ultrasound examination.

**Inclusion criteria are:**

Patients aged from 18 to 60 years.Live fetus at gestational age ≥ 36 weeks.Singleton or multiple pregnancy.Mentally competent.American Society of Anesthesiologists (ASA) physical status I–III.Subject is planning cesarean section under general anesthesia and tracheal intubation at our maternity at Sichuan Provincial People's Hospital.Informed and written consent.

**Exclusion criteria are:**

Abnormal pharynx or anatomy.Expected difficult laryngoscopy with cervical spine abnormality, maxillofacial anomalies, upper airway disease, a history of previous difficult intubation.Pregnancies ending with a stillborn.Women presenting for the study but who have been previously included in the study in a previous pregnancy.Women who are unconscious, severely ill, those with learning difficulties, or mentally handicapped.

### Outcome measures

3.4

Primary outcomes:

Ultrasound measurements: thickness of anterior cervical soft tissue at five levels: distance (cm) from skin to the trachea at hyoid bone, epiglottis, cricothyroid membrane, thyroid isthmus, suprasternal notch level.Cormack–Lehane grade

Secondary outcomes:

Body mass index (BMI), Mallampati score, neck mobility (flexion/extension degrees from midline), upper lip bite test, jaw movement, mouth opening (cm), thyromental distance (cm), sternomental distance (cm), hyomental distance (cm) and neck circumference (cm) at the level of the thyroid cartilage.

### Preoperative evaluation and ultrasonography

3.5

Preoperative evaluation and ultrasound examination were performed one day before the surgery, data was obtained in standard fashion. The patient's information, medical history was obtained. Physical examination include height, weight, body mass index (BMI). Airway evaluation include Mallampati score, neck mobility (flexion/extension degrees from midline), upper lip bite test, jaw movement, prominent incisor. A flexible ruler will be used to measure airway parameters, mouth opening (cm), thyromental distance (cm), sternomental distance (cm), hyomental distance (cm) and neck circumference (cm) at the level of the thyroid cartilage.

The thicknesses of the anterior neck soft tissues were measured with a portable ultrasound machine (M7 Super; Mindray, Shenzhen, China). A 6 to 13 MHz high frequency curvilinear ultrasound transducer was used for ultrasound scanning. Patients will be explained about the ultrasonography procedure and positioned in supine with the head in a neutral position. Ultrasonography with the probe placed in the transverse axis, craniocaudal sagittal scan, submental region of the neck. The distances were measured at five levels (hyoid bone, epiglottis, cricothyroid membrane, thyroid isthmus and suprasternal notch) with normal and extended neck position in the median axis. Figure 2A–E showed the ultrasonography procedure:

A.measure the distance from the skin to the hyoid bone;B.distance from the skin to the epiglottis performed at the thyrohyoid membrane level;C.distance from skin to anterior commissure of the cricothyroid membrane;D.distance from skin to thyroid isthmus;E.distance from skin to the trachea at suprasternal notch level. The images will be retrieved from ultrasound machine and stored on computer.

**Figure 2 F2:**

Ultrasound measurement the anterior cervical soft tissue thickness at five anatomical levels (A) hyoid bone, (B) epiglottis, (C) cricothyroid membrane, (D) thyroid isthmus, (E) suprasternal notch. Consent to publish the figure was obtained from the patient.

### Anesthesia procedure

3.6

On the operation day, standard monitoring of electrocardiogram, pulse oximetry, noninvasive blood pressure will be performed throughout anesthesia to detect clinical vital signs. Train-of-four (TOF) were used for neuromuscular monitoring. Patients will fasting for 8 hours, clear fluids may be given up to 2 hours preoperatively before anesthesia. Ranitidine (150 mg), a H2-receptor antagonist was administrated the night before and two hours before anesthesia for stomach preparation. Equipment for managing the difficult airway will be ready for use. General anesthesia was administered after the disinfection and towel laying procedures, obstetricians are standby for cesarean section. Rapid sequence anesthesia induction was recommended for obstetric anesthesia and will be performed as standard protocol.^[14]^ Preoxygenation was performed for 3 min through a face mask, propofol (2 mg/kg) was administered, then a neuromuscular blocker (rocuronium 1 mg/kg) was given.

### Laryngoscopy

3.7

When the anesthetic depth was enough, and TOF indicated neuromuscular blockade was deemed as adequate (TOF 1/4 0), the anesthesiologists with more than 5 years of experience perform the laryngoscopy and endotracheal intubation. Patients will be in a standard sniffing position, Macintosh curved laryngoscope blade will be used to perform direct laryngoscopy and intubation. A modified version of the Cormack–Lehane grade will be used to evaluate difficult airway.^[15]^ The Cormack–Lehane grades 1 or 2a will be designated as “easy”, grades 2b or 3a, and grades 3b or 4 represent “restricted or difficult” laryngoscopies: grade 2b (only arytenoids visible), 3a (only epiglottis visible and liftable), 3b (epiglottis adherent to pharynx) and 4 (no laryngeal structures seen). A maximum of three attempts will be permitted. In addition, if the SpO2 decrease to less than 90% or patients with unanticipated difficult ventilation or intubation will be withdrawn from the study. Steps followed the process in the guidelines of the Obstetric Anesthetists’ Association and the Difficult Airway Society will be taken immediately.^[6,14]^ LMA will be utilized to maintain ventilation. If the SGA failed, cricothyroid membrane puncture will be performed immediately. The proper capnograph waveform could confirm the tracheal intubation. The attending anesthesiologist performs the further anesthetic management of the patient.

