## Discussion

4

The maternal mortality has been reduced over the past four decade, but, the rate of failed tracheal intubation has remained unchanged in obstetrics anesthesia. Parturient have high risk of difficult airway due to the physically airway anatomy changes in the upper respiratory tract. Like obese patients, decreased functional residual capacity and increased oxygen requirements accelerate the onset of desaturation during apnea.^[1]^ In 2015, China's one-child policy was replaced by a universal two-child policy. Sichuan Provincial People's Hospital is the center of clinical service and research, one of National Top Hundred Excellent Hospitals in China. Since 2015, more elderly and critically ill parturient were received in our hospital, and need to cesarean section with general anesthesia. Accurate airway assessment is the first step towards avoiding potential complications and should always be the most important in airway management. Unfortunately, current clinical predictors such as the Mallampati score, thyromental distance had low sensitivity and high variability for detecting a difficult airway. Ultrasound is a high-frequency sound wave, it is bedside, radiation-free, cheap, fast and accurate, is the best choice in obstetric anesthesia. Previous study found that ultrasound distances from the thyroid isthmus to skin surface, the minimum distance from the hyoid bone to skin surface, the minimum distance from skin to anterior commissure of the vocal cords, the minimum distance from skin to trachea at the level of the jugular notch and the distance from skin to epiglottis midway can predict the difficult airway in non-obstetric patients.

This is likely the first study to find whether preoperative ultrasound assessment of neck anatomy can predict difficult airway in parturient. The limitations are,

1)in order to ensure patient safety, patients with unexpected and complicated difficult airway management will be withdrawn from the study, that might cause a potential selection bias.2)this is a single-center observation study in Chinese people, the extrapolation of our findings to other centers and race of people needs further evaluation.

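### Section 3.7 withdraws women on undefined triggers that overlap the outcome, so an unknown, mainly severe share of the difficult cases leaves the analysis

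*Protocol article*

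**What the plan says.** The Objective is to "find whether preoperative ultrasound assessment of neck anatomy can predict difficult airway in parturient". Section 3.7 (Laryngoscopy) sets the reference standard: "A modified version of the Cormack–Lehane grade will be used to evaluate difficult airway". Grades 1 and 2a count as easy, and 2b and worse as restricted or difficult. Section 3.9 uses the same threshold (grade 2b or worse) and asks for 20 events. Section 3.10 (Statistics) then compares easy with difficult intubation and plans ROC curves and logistic regression.

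Section 3.7 also contains the withdrawal rule: "if the SpO2 decrease to less than 90% or patients with unanticipated difficult ventilation or intubation will be withdrawn from the study". It defines neither unanticipated nor difficult intubation. The first limitation in the Discussion returns to the rule: "patients with unexpected and complicated difficult airway management will be withdrawn from the study, that might cause a potential selection bias".

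Two other provisions bear on who is left to trigger it. Section 3.3 excludes at entry "Expected difficult laryngoscopy with cervical spine abnormality, maxillofacial anomalies, upper airway disease, a history of previous difficult intubation". It also says of the anesthesiologists who perform laryngoscopy that "they will be blinded to the findings of ultrasound examination". Section 3.10 places data collection after intubation is complete.

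**The concern.** Whether a woman is analysed depends on what happens during her airway management, which is close to what the study sets out to predict. Some causes of expected difficulty are removed at entry, and the ultrasound result cannot alert the laryngoscopist. Much of the difficulty that remains may therefore come as a surprise and meet the trigger. Because the trigger is undefined, the operator decides case by case who goes.

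Two things are at stake. The first is the number of events, which is small even without withdrawals. The second is the mix of cases: if the severest go, sensitivity, AUC, predictive values and odds ratios describe a milder group than the one that matters for safety. The SpO2 trigger may add selection on body habitus, since the Discussion likens parturients to obese patients in how fast they desaturate.

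**Working it through.** **Inputs from section 3.9.** Incidence of difficult intubation p = 10–20%; target sensitivity at least 80%; 20 events needed; 106 evaluable women; 20% dropout; 127 recruited. The share w of difficult cases withdrawn is not given, so a range is shown.

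**The plan's own figures.** 106 × 1.2 = 127.2, which gives 127. The 106 does not follow from the stated inputs: 20/0.20 = 100, 20/0.15 = 133.3 (so 134), 20/0.10 = 200. It fits an unstated incidence of 20/106 = 18.9%. The present point does not depend on how 106 was obtained.

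**Events left.** Expected events = N × p × (1 − w), with N = 106:

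| p | w = 0 | 10% | 25% | 50% | 75% |
|---|---|---|---|---|---|
| 10% | 10.6 | 9.5 | 8.0 | 5.3 | 2.7 |
| 15% | 15.9 | 14.3 | 11.9 | 7.9 | 4.0 |
| 20% | 21.2 | 19.1 | 15.9 | 10.6 | 5.3 |

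At the most favourable stated incidence, losing one difficult case in ten already takes the expected count below 20. If none of the dropout allowance were used for anything else, 127 women at 20% would give 127 × 0.20 = 25.4 events, and losing a quarter of these leaves 19.1. The allowance is sized for losses spread over all women; these fall on the cases.

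**Effect on accuracy (illustrative).** Latent severity L is standard normal, and thickness X = ρL + √(1 − ρ²) × noise. Difficult means the top 15% of L. The cut-off on X is fixed where true sensitivity is 80%, and the severest share w of difficult cases is then removed. Both ρ and the choice of the severest cases are assumptions.

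| ρ | Measure | w = 0 | 25% | 50% | 75% |
|---|---|---|---|---|---|
| 0.5 | AUC | 0.757 | 0.734 | 0.719 | 0.706 |
| 0.5 | Sensitivity | 80% | 77.2% | 75.1% | 72.9% |
| 0.6 | AUC | 0.810 | 0.785 | 0.769 | 0.754 |
| 0.6 | Sensitivity | 80% | 76.5% | 73.8% | 71.6% |

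AUC falls by 0.757 − 0.734 = 0.023 at the least and 0.810 − 0.754 = 0.056 at the most. Repeat runs agree to about 0.003.

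**Specificity and predictive values.** Specificity at a fixed cut-off is computed in easy-view women only, so removing difficult cases leaves it unchanged. With 20% incidence, ρ = 0.5 and half of the cases withdrawn, it stays at 0.546. It moves to 0.557 if about 3% of easy-view women, more often those with thick necks, are also withdrawn for SpO2. In the same setting without that SpO2 loss, PPV falls from 0.31 to 0.17 and NPV rises from 0.92 to 0.95.

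**The case against.** The strongest defence is that the trigger and the outcome are different things. The outcome is a laryngoscopic view. The trigger stands between the limit of three attempts and the rescue sequence, and the Discussion narrows it to complicated management. A woman with grade 2b or 3a who is intubated within the permitted attempts plausibly stays in. This stands. A reader might infer that the rule deletes the outcome, or empties the difficult group so that no ROC curve can be built. That holds only if every grade of 2b or worse counts as unanticipated difficult intubation, which the documents do not say.

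A reader might also infer that almost every remaining difficult case is unanticipated. Section 3.3 excludes expected difficulty from listed causes only. High BMI, a high Mallampati score and a large neck circumference are not listed, and the stated blinding covers ultrasound findings, not bedside tests. Nor is every accuracy estimate biased, as the specificity result shows.

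The simulated bias is modest beside sampling error. With 16 events, the 95% half-width around a sensitivity of 80% is 1.96 × √(0.8 × 0.2/16) = 0.196, about 20 points. In the simulation the bias also understates ultrasound, so it would not manufacture a positive result. This stands too, and it makes the loss of events the weightier consequence.

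Lastly, the authors disclose the bias, and the flow chart and data table are not visible here. Disclosure does not repair the rule. Selection bias arises only if these women are not analysed, so the limitation indicates that the authors expect to lose them.

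**Conclusion.** The point holds in limited form. As written, the plan removes from analysis an undefined and probably mainly severe subset of the difficult cases, on triggers that overlap the outcome. The event arithmetic rests on the protocol's own incidence and event target; only the withdrawn share is assumed. Losing half of the cases would leave 5.3–10.6 events of 106 against 20 required. The falls of about 0.02–0.06 in AUC, and in sensitivity from 80% to about 72–77%, are illustrative. They depend on the assumed correlation, the 15% incidence and the severest cases going first; the direction could differ if other women were withdrawn.

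Much of the loss is avoidable. Ultrasound is done the day before surgery, and the grade is read at laryngoscopy. It would be too strong to say that both results always exist at the trigger: desaturation or difficult ventilation can come before any view is obtained.

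**What to change.** Leave all rescue steps as they are and separate leaving study procedures from leaving the analysis:

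- In 3.7 and 3.10, state that women who meet a trigger leave study procedures only, and that their ultrasound, clinical and laryngoscopy data are retained.
- Analyse them in the main analysis by the Cormack–Lehane grade at first laryngoscopy.
- Where no grade was obtained, treat it as missing in the main analysis and count it as difficult in a sensitivity analysis only. Counting it as difficult in the main analysis would relabel desaturation or difficult ventilation as a poor view. It could also flatter ultrasound if BMI drives both desaturation and neck thickness.
- Report the number meeting each trigger, and how many of them had a grade.
- Revise the first limitation in the Discussion so that it covers only the ungraded women.

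The cost is a few sentences, with no change to care, no extra procedure and no extra patients. The change has to be made prospectively, because a grade that was not recorded cannot be recovered. It does not cure the shortfall at lower incidence: with every case kept, 106 women still give only 10.6 events at 10%.
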